### Data management

Data will be entered in a CRF by the investigator or a designated representative of the respective center. Participant names and collected data are subject to medical confidentiality. In the case of resignation, collected data may be pseudonymized unless the participant explicitly requests that all data be erased. Data will be entered into the CRF as soon as possible after data retrieval. After completion, the original CRF will be sent to the SDGC for validation and transfer into the trial database. Double data entry will be performed in order to ensure accurate transfer from the CRF to the database. At the end of the trial, the original CRFs and final database will be archived by the principal investigator, who is responsible for providing data to trial investigators. All trial members are obliged to ensure the deletion of duplicate data recordings at the end of the trial.

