### Statistical methods

#### Sample size

Sample size was determined for the primary endpoint, the intensity of pain during mobilization measured on the VAS 24 hours after surgery. Park *et al*. reported a mean (± standard deviation) VAS score of 4.2 ± 1.7 for transvaginal hybrid NOTES vs. 5.7 ± 1.7 for conventional laparoscopic right-sided hemicolectomy
[10]. According to Gallagher *et al*. a standardized effect size of unity in the VAS score (difference in unity given a standard deviation of unity) is discriminable by patients and can be considered clinically relevant
[25]. We made the following assumptions when calculating the patient number:

 Hypothesis: transvaginal hybrid NOTES sigmoid resection causes less pain than laparoscopic-assisted sigmoid resection 24 hours after surgery (superiority analysis). Two-sided analysis with a type I error (α) of 0.05 and power (1-β) of 0.90. The standardized effect size was assumed to be 1 (difference in VAS of 1 and standard deviation of 1). The power was set at 0.90 because some evidence is already available.

Based on these assumptions, a sample size of 23 patients per arm was calculated using the R package (version 0.1-8;
http://cran.r-project.org/web/packages/Sample.Size/index.html, *t* test for two independent samples). Assuming a drop-out rate of 20%, the total number of patients needed per arm is 29, resulting in a total patient number of 58 patients for the primary arm.

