#### Statistical analysis

Statistical analysis will be performed using the R statistical software (
http://www.r-project.org). A two-sided *P* value <0.05 will be considered significant. For baseline characteristics, descriptive statistics will be used. For analysis of the primary outcome, a Mann-Whitney *U* test will be applied. For categorical secondary endpoints, chi-square statistics will be used. To compare continuous secondary endpoints (operating time, length of hospital stay, analgesic use, time to return to normal activity), Mann-Whitney *U* tests will be applied. No interim analysis is planned for this study. For the time course of pain at provocation and at rest, a mixed model with mean VAS scores will be applied.

Missing values will be replaced with the last available value (the last observation carried forward (LOCF) approach). Data from patients who withdraw from the study will be disregarded unless exclusion is based on postoperative patient wishes and the patient agrees to the use of the already obtained data.

The confirmatory analysis will be performed based on intention-to-treat (ITT) patients and with respect to ITT principles. A standard sensitivity analysis will be performed on the per-protocol population.

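### The withdrawal rule discards data already recorded on randomized patients, so the confirmatory analysis as written is not intention-to-treat

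*Protocol article*

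**What the plan says.** Three statements in the protocol article bear on this.

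- **Statistical analysis, withdrawal rule:** "Data from patients who withdraw from the study will be disregarded unless exclusion is based on postoperative patient wishes and the patient agrees" to use of the data already obtained. The default is deletion. The exception has two conditions, and both must be met.
- **Statistical analysis, next paragraph:** "The confirmatory analysis will be performed based on intention-to-treat (ITT) patients and with respect to ITT principles". The only sensitivity analysis named is this: "A standard sensitivity analysis will be performed on the per-protocol population".
- **Data management:** "In the case of resignation, collected data may be pseudonymized unless the participant explicitly requests that all data be erased". Here the default is that data may be kept, and removal needs a request.

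Missing values are handled in the same section as the withdrawal rule: "Missing values will be replaced with the last available value (the last observation carried forward (LOCF) approach").

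**The concern.** ITT compares all randomized patients in the arms to which they were allocated. The withdrawal rule removes two groups from that set:

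- patients excluded on any ground other than their own postoperative wish, whatever has already been recorded on them;
- patients who withdraw themselves and do not give agreement.

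Both criteria are settled after randomization, so membership of the analysed set can depend on arm or outcome. If it does, the randomized comparison is no longer protected for the primary endpoint. Morbidity is more exposed, because it is collected up to 36 months. A result obtained this way could not properly be reported as ITT.

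The protocol states this rule outright. It is therefore not a detail left to an analysis plan that is not shown.

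**Working it through.** **1. When the rule can act**

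| Event | Time | Section |
|---|---|---|
| Randomization | During surgery, after diagnostic laparoscopy | Randomization, allocation concealment, and blinding |
| Primary VAS | 24 hours after surgery | Primary endpoint |
| Discharge | POD 5 at the earliest | Discharge criteria |
| Planned unblinding | Removal of the dressing at discharge | Randomization, allocation concealment, and blinding |
| Last follow-up | 36 months | Perioperative management, discharge, and follow-up |

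Most of the time in which a patient can leave therefore comes after the 24-hour score is on file, and most of it comes after unblinding. A patient who leaves at month 12 without agreeing to data use would lose a valid score that was recorded blind.

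**2. Whether anything else in the plan restores these patients**

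It does not. LOCF needs a retained earlier value, and a patient whose data are disregarded has none. The per-protocol analysis does not bring deleted patients back. The drop-out allowance adds numbers, so it protects power and not comparability.

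**3. The plan's own sample size**

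Inputs (Statistical methods, Sample size): a two-sided 5% level, 90% power, and a VAS difference of 1 with SD 1, which is a standardized effect of 1.

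- The two-sample t test needs 22.02 per arm, hence 23. Power is 0.8997 at 22 and 0.912 at 23.
- Drop-out: 23 / (1 − 0.20) = 28.75, hence 29 per arm and 58 in total. The stated figures reproduce.
- The allowance is 0.20 × 29 = 5.8, about 6 patients per arm.

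**4. What deletion could do to the primary test**

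The documents give no withdrawal pattern, so the patterns below are assumed. Set-up: normal VAS with SD 1, 29 per arm, no true difference, two-sided Mann-Whitney test at 0.05, 20,000 simulated trials per row. The simulation standard error near 0.05 is √(0.05 × 0.95 / 20,000) = 0.0015. Control-arm deletions are random and equal in number. Bias is in VAS points at SD 1, in favour of NOTES.

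| Experimental-arm deletions | Deleted per arm | Type I error | Bias |
|---|---|---|---|
| None | 0 | 0.045 | 0.00 |
| Completely at random | 6 | 0.047 | 0.00 |
| Random within the upper half of pain scores | 3 | 0.057 | 0.09 |
| Random within the upper half of pain scores | 6 | 0.095 | 0.19 |
| Exactly the highest scores | 3 | 0.105 | 0.19 |
| Exactly the highest scores | 6 | 0.229 | 0.35 |

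If the highest scores are removed from one arm and the other keeps all 29, the error is about 0.10 (3 removed) and 0.25 (6 removed). The last bias agrees with theory: removing the top 20% of a normal distribution lowers its mean by φ(0.8416) / 0.80 = 0.350 SD. The mirror-image pattern would bias the result against NOTES.

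**5. Effect of the fix on power (true difference 1 SD)**

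| Analysed per arm | t test | Mann-Whitney (simulated) |
|---|---|---|
| 29 (all kept) | 0.963 | 0.953 |
| 23 (6 lost at random) | 0.912 | 0.891 |

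Keeping the patients needs no new sample size.

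**The case against.** The strongest reply is that the rule is narrower than it looks.

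- **Own withdrawal.** Patients are randomized during surgery, so a patient's own later withdrawal is in effect always postoperative and meets the first condition. What remains is her agreement to data use, which is a consent safeguard. Any acceptable rule must also honour a request for erasure. This stands in part: honouring explicit erasure is no flaw. The flaws are deletion when she says nothing, and deletion when the exclusion does not rest on her wish.
- **Grounds for exclusion.** A reader might infer that patients with complications or conversions will be deleted. The documents do not say so. Conversion appears only as a reason not to enrol, and complications and adverse events lead to unblinding, not removal. The rule speaks of exclusion and implies grounds other than patient wish, but it names none.
- **Non-random deletion.** A reader might also infer that informative deletions will occur. The text permits them but does not show that they will happen.
- **Data management.** A reader might call this a flat contradiction. The sentence is permissive, concerns data handling, and does not define the analysis set. It suggests a different default, and no more than that.
- **Exposure and scale.** Few patients can leave before 24 hours, and both sides are blinded then. Nothing says that the whole 20% allowance would be deleted under this rule. Bias should be set against the planning difference of 1 with SD 1; the 1.5-point difference is the cited matched cohort's result. The error rates of 0.10 to 0.25 describe an extreme case.

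These points limit the likely size. They do not reconcile the deletion rule with the ITT claim.

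**Conclusion.** The concern holds as a conflict between two stated rules. Followed literally, the withdrawal sentence produces an analysis set that is not ITT, and nothing else in the plan repairs this. That conclusion rests on the text and on the timing of randomization, not on the simulation.

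The size is unknown. It could be nil if few patients leave or if deletions are unrelated to arm and pain. With the moderate patterns assumed above, the bias is 0.09 to 0.19 points, or 9% to 19% of the planning difference. The extreme pattern with 6 per arm reaches 0.35 points, or 35%, and is an upper illustration, not an expectation. These figures assume normal scores, SD 1 and 3 to 6 deletions per arm.

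The difference from the Data management section is a secondary point, to be settled in the same revision.

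**What to change.** Replace the withdrawal sentence in the Statistical analysis section with wording to this effect:

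> The ITT set comprises all randomized patients, analysed in the arm to which they were allocated. Withdrawal or exclusion, whoever initiates it, ends further data collection only. All data obtained up to that point, including the 24-hour VAS, are used unless the patient explicitly requests erasure. Withdrawals and erasures are reported by arm, with reason and timing.

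Bring the Data management section into line with the same opt-out rule. If any 24-hour scores are erased or missing, a worst-case or tipping-point analysis would show whether they could change the conclusion; the per-protocol analysis cannot.

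The cost is a wording change in two sections and a check that the patient information and consent form, which are not shown, allow data to be kept by default. If they do not, the consent text must be dealt with first. The sample size is unaffected. The change should be made before any outcome data are seen by arm.

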### Ethical approval

The ethics committee of the University of Heidelberg reviewed and approved this study on January 13, 2014 (reference number: S-608/2013).

### Good clinical practice

The trial was conceived and will be conducted according to all relevant national and international rules and regulations, such as the guidelines for good clinical practice by the ICH-GCP
[24] and Declaration of Helsinki (2013)
[26].

### Dissemination policy

The results of the TRANSVERSAL trial are intended to be presented at international medical congresses on corresponding fields of interest, for example, general and visceral surgery or endoscopic surgery. Written publications are planned within surgical or endoscopic scientific journals. The authorship for written publications has to be confirmed unequivocally by all lead investigators and will only be granted in the case of substantive contributions to the design, conduct, data analysis, and interpretation. The contact data for all lead investigators and access to the full study protocol will be presented online on the website of the surgical department of the University of Heidelberg (
http://www.klinikum.uni-heidelberg.de/Chirurgische-Klinik.1010.0.html). After completion of the full study report, anonymized participant-level datasets and the statistical code for generating results will be available by contacting the principal investigator.

### Registration

The study protocol has been registered with the German Clinical Trials Register (
https://drks-neu.uniklinik-freiburg.de/drks_web/) under the registration number DRKS00005995.

### Protocol version

This manuscript refers to the fourth version of the full study protocol issued on August 26, 2014. Protocol modifications will be reported to all investigators, the local ethics committee, the German Clinical Trials Register, all trial participants, and the journal.

## Discussion

NOTES represents a consequence of developing minimally invasive surgery to reduce abdominal wall trauma using natural orifice access to the peritoneal cavity. Laparoscopic-assisted surgery may eventually advance to pure laparoscopic surgery, as minilaparotomy can be avoided by using the natural orifice for specimen retrieval. Since the white paper in which members of the Society of American Gastrointestinal and Endoscopic Surgeons (SAGES) and American Society for Gastrointestinal Endoscopy (ASGE) presented future requirements for the development and clinical application of NOTES, clinical and experimental studies have focused on feasibility
[27]. Although transvaginal NOTES procedures have already entered the clinical routine, only a few studies have compared NOTES to current standard surgical treatment
[10, 28, 29].

Pain intensity 24 hours after surgery has been chosen as a primary endpoint of TRANSVERSAL trial because pain is one of multiple outcomes reflecting trauma and recovery after abdominal surgery
[30]. In contrast to other factors, pain may be objectified well using the VAS, a test with high validity
[31]. Finally, because pain affects a variety of physiological processes, such as the stress response, inflammation, and wound healing, we think that pain may represent a decisive factor within the recovery process. We decided to measure pain intensity during mobilization of the patient because, even under closely monitored analgesic treatment, pain may be provoked by mobilization and affect postoperative patient mobility. The secondary endpoints of the TRANSVERSAL trial comprise additional outcomes reflecting recovery, such as postoperative patient mobility measured by an electronic pedometer, quality of life, length of hospital stay, and time to return to normal activity.

To the best of our knowledge only three randomized controlled trials have compared transvaginal hybrid NOTES to laparoscopic surgery, and all of the studies assessed the transvaginal NOTES technique applied to cholecystectomy
[28, 29, 32]. In 60 female patients, Noguera *et al.* found no differences with regard to morbidity, postoperative pain, length of stay, and time off work for hybrid transvaginal NOTES, hybrid transumbilical NOTES, and conventional laparoscopic cholecystectomy at 1-year follow-up. In contrast, in a recent randomized controlled trial including 40 female patients, Bulian *et al*. found that the transvaginal hybrid NOTES technique is associated with less postoperative pain, less analgesic use, and improved postoperative quality of life compared to needlescopic three-trocar cholecystectomy in the short term (POD 1 to POD 10). Borchert *et al*. found no significant difference between transvaginal hybrid NOTES and laparoscopic cholecystectomy with regard to postoperative pain and safety in 97 patients in the short term (POD 1 to POD 7).

With regard to colorectal surgery, clinical evidence for NOTES procedures is limited to cohort studies and one matched controlled study. Cohort studies have shown the feasibility of transvaginal and transanal specimen extraction for colonic resection
[11, 33–35]. In a matched cohort study including 68 patients, Park *et al*. found that transvaginal specimen extraction for right-sided hemicolectomy is associated with less pain and shorter hospital stay than the laparoscopic-assisted technique. No difference was found with regard to morbidity after a median follow-up of 23 months
[10].

Despite increasing clinical application, NOTES has still encountered broad skepticism because its potential benefits are generally doubted and potential access-related complications feared. The TRANSVERSAL trial is the first study comparing NOTES to conventionally assisted surgery for colonic resection in a randomized controlled setting. The results of this trial will provide valuable clinical evidence for objective assessment of the potential benefits and risks of NOTES procedures compared to the current surgical standard.

## Trial status

Recruitment will begin in the fourth quarter of 2014.

## Abbreviations

CRF: case report form
ICH-GCP: guidelines for good clinical practice constituted by the International Conference on Harmonization of Technical Requirements for Registration of Pharmaceuticals for Human Use
ITT: intention-to-treat
NOTES: natural orifice transluminal endoscopic surgery
POD: postoperative day
SAE: serious adverse event
VAS: visual analogue scale.
